# What is the impact of psychiatric decision units on mental health crisis care pathways? Protocol for an interrupted time series analysis with a synthetic control study

**DOI:** 10.1186/s12888-020-02581-5

**Published:** 2020-04-23

**Keywords:** Interrupted time series, Synthetic control, Mental health crisis, Service pathways, Service parameters, Psychiatric decision unit, emergency department, crisis management, inpatient alternatives, psychiatric crisis

## Abstract

**Background:**

The UK mental health system is stretched to breaking point. Individuals presenting with mental health problems wait longer at the ED than those presenting with physical concerns and finding a bed when needed is difficult – 91% of psychiatric wards are operating at above the recommended occupancy rate. To address the pressure, a new type of facility – psychiatric decision units (also known as mental health decision units) – have been introduced in some areas. These are short-stay facilities, available upon referral, targeted to help individuals who may be able to avoid an inpatient admission or lengthy ED visit. To advance knowledge about the effectiveness of this service for this purpose, we will examine the effect of the service on the mental health crisis care pathway over a 4-year time period; the 2 years proceeding and following the introduction of the service. We use aggregate service level data of key indicators of the performance of this pathway.

**Methods:**

Data from four mental health Trusts in England will be analysed using an interrupted time series (ITS) design with the primary outcomes of the rate of (i) ED psychiatric presentations and (ii) voluntary admissions to mental health wards. This will be supplemented with a synthetic control study with the same primary outcomes, in which a comparable control group is generated for each outcome using a donor pool of suitable National Health Service Trusts in England. The methods are well suited to an evaluation of an intervention at a service delivery level targeting population-level health outcome and the randomisation or ‘trialability’ of the intervention is limited. The synthetic control study controls for national trends over time, increasing our confidence in the results. The study has been designed and will be carried out with the involvement of service users and carers.

**Discussion:**

This will be the first formal evaluation of psychiatric decision units in England. The analysis will provide estimates of the effect of the decision units on a number of important service use indicators, providing much-needed information for those designing service pathways.

**Trial registration:**

primary registry: isrctn.com Identifying number: ISRCTN77588384 Link: Date of registration in primary registry: 27/02/2020.

## Background

Mental health crisis care is under extreme pressure internationally [1–5]. In the UK, bed occupancy is high, staff are under pressure and resources are constrained – the UK Emergency Department (ED; also known as Accident and Emergency) system has been described as near breaking point [6]. In the UK, two-thirds of people attending the ED multiple times for any reason have had previous contact with specialist mental health services or have previously been admitted to an acute hospital for a mental health condition [7], with frequent attenders at greater risk of psychiatric inpatient admissions [8]. People presenting with a mental health issue are over 6 times more likely than people presenting with a physical concern to wait more than 4 hours at the ED [9]. Bed occupancy in inpatient psychiatric facilities is well above recommended levels with 91% of wards operating above the recommended occupancy rate [10]. Mental disorders are estimated to account for around 5% of ED attendances in the UK and almost 30% of acute inpatient bed occupancy and acute readmissions [7, 9, 10]. Although the emergence of liaison psychiatry services has enabled organisations to provide responsive mental health advice and assessment within emergency care settings, there remain wide variations in service provision [11] and ongoing challenges to sustainability [12]. The introduction of crisis resolution and home treatment teams and triage wards has offered little benefit in reducing contact with acute services, inpatient admissions or costs across the wider in-patient system compared with standard models of care [13–15], with ongoing staff concerns over the accuracy of triage decisions for mental health presentations [16, 17], while inpatient care remains unpopular, expensive and sometimes detrimental for individuals and their families [7, 18–20].

### Study setting

This research takes place in four geographical locations in England, each of which have an PDU. To maximize generalisability, sites have been chosen where there is variation in the configuration of the PDUs across the four sites to allow comparison and ascertain the optimal PDU configuration (see Table 1).

**Table 1 Tab1:** Structural variation in Psychiatric Decision Units

Trust with PDU	Maximum Length of Stay	Capacity	Referral route
Inner city 1	48 h	5	ED (liaison), Crisis Resolution and Home Treatment Teams, Street Triage
Inner city 2	24 h	10	ED (liaison), Out of Hours Team, Approved mental health professionals team, Mental health inpatient wards, 136 Place of Safety, Community teams, including crisis resolution and home treatment teams
Inner city 3	72 h	8	ED (liaison), Street Triage
Rural Site	24 h	6	ED (liaison), Crisis Resolution and Home Treatment Teams

Referrals to PDU can be made from a range of services including ED liaison psychiatry teams, Crisis Resolution & Home Treatment teams and street triage teams. Referrals are triaged at a decision point prior to admission to the PDU. Overnight accommodation is single sex and units tend to be small, with a staff: service user ratio of at least 1:2 to allow substantial time for detailed assessment, brief intervention and onward referral/ signposting. Therapeutic work is typically cognitive or psychosocial, for example, improving resilience and solution focused approaches. Pathways from the decision unit can be either subsequent admission, discharge or forward signposting to appropriate recovery and preventative services.

### Aims

The aim of the study is to identify the impact of psychiatric decision units on mental health crisis care pathways. We will do this by administering an interrupted time series, supplemented by a synthetic control study, using routinely collected mental health trust and emergency department data. We will produce estimates of the extent to which changes in key service parameters (e.g., informal psychiatric admissions and mental health presentations at the ED) in the pre- and post-interruption period are explained by the introduction of PDUs at each of the sites in the study, and combine the results across sites to give a generalizable effect size estimate.

## Methods

### Study design

We will use an interrupted time series design, supplemented by a synthetic control study [32]. Adults (over 18) in psychiatric crisis in England of both sexes are eligible. The data collection periods started in November 2012 and will end on March 31st 2020. This project has been given favourable opinion from the East Midlands Leicester South Research Ethics Committee (19/EM/0226) and entry to the study is currently open. The research is funded by the National Institute of Health Research (NIHR) Health Services and Delivery Research (17/49/70). The current protocol described is version 4.0, dated 16th December 2019, and relevant parties will be informed of any important protocol modifications. The research uses aggregate service use data, and so Trusts, rather than individuals join the study. A data monitoring and ethics committee is not needed as there is no experimental intervention. The Independent Steering Committee (which includes an academic chair, a statistician, and two public and patient members) provides oversight and advice.

An interrupted time series (ITS) design, using routinely collected healthcare data, will explore change in acute and psychiatric hospital activity after the introduction of PDUs in our 4 sites, hereafter referred to as the treated trusts. Quasi-experimental methods, such as an ITS design, are appropriate when the randomisation and/or the ‘trialability’ of the intervention is limited. They are particularly well suited to evaluations of organisational interventions or changes to health care at a delivery level that target population-level health outcomes and when a time series is available, as in this instance [33, 34]. In ITS studies, data are collected at multiple time points before and after the introduction of a change or intervention; enabling detection of whether or not the change has a significantly greater effect on outcomes of interest than any underlying secular trend [35]. ITS findings primarily concern whether the level and/or slope of the outcome measurement is altered once change has been implemented. Advantages of the method include controlling for baseline variation, periodicity, cyclical trend and/or autocorrelation in the time series design, prior to examination of change effects. The number of observations is important; examining a long series of outcome measurements more readily allows analyses to track both immediate and delayed effects [36].

A synthetic control study in which comparative control trusts (in which no change in service delivery/ model of care occurs) are included in an interrupted time series analysis, improves the specificity of the evaluation and better controls for secular trends over the baseline, change or intervention, and follow-up periods [34]. Advanced synthetic control methods [37] will be used for controlled analysis to estimate a robust counterfactual against which to compare the impact of the introduction of each of the four participating PDUs on outcome variables. A mapping study will be used to identify suitable control trusts for the synthetic control study (sites without a PDU). A timeline of changes to the crisis care pathway will be elicited through interview with key informants and will be used to interpret the analyses.

### Sample size: ITS

The weekly series for 24 months pre- and post-implementation of PDUs (208 weekly or 48 monthly time points) is more than the 40 data points (20 pre- and 20 post-change) typically considered as adequate for valid ITS model analysis [38], and provides sufficient power to detect medium effects where they exist. For example, to detect a time x slope interaction with medium effect size on an outcome, a sample of 208 time points has > 99% power (assuming one parameter tested and no more than five factors entered in model; calculated using G-Power, ‘linear multiple regression: fixed model, r^2^ increase’ module).

### Sample size: synthetic control study

The monthly series for 24 months pre- and 24 months post-implementation of PDUs (including a one-month ‘bedding in month’), yields 49 time points. This provides us more than the 40 data points (20 pre- and 20 post-change) typically considered as adequate for valid ITS model analysis [38], and provides sufficient power to detect medium effects where they exist.

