#### Synthetic control study

For the synthetic control study, aggregated service use data over the relevant 49 months for both the treated trusts and the selected control trusts will be sourced from Hospital Episodes Statistics (HES) and the Mental Health Services Data Set (MHSDS). The relevant time period is 49 months, as the month following the introduction of the PDU is excluded from the analysis to allow a bedding in time for set-up. HES and MHSDS are databases recording all admissions, outpatient appointments and ED attendances at NHS hospitals in England and mental health NHS trust service use respectively (NHS Digital, [42]).

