## Analytical strategy

### Interrupted time series

We will use segmented regression analysis of interrupted time series data [34, 43] for the ITS. This approach minimizes threats to internal validity while maximizing external validity by taking into account any serial correlation, background variation and underlying trends independent of the intervention over time. Segmented regression analysis is the most common method used in ITS of healthcare interventions [44] and has previously been successfully used to predict emergency department (ED) presentations and hospital admission [45, 46], including psychiatric admissions and mental health-related ED visits [47].

Initially, for each outcome, to check for serial auto-correlation due to repeated measures, we will examine the plot of residuals from regression analyses and use the Durbin-Watson test [48]. Where no significant autocorrelation is detected, we will use a simple time series regression model. If significant autocorrelation exists, we will investigate several autocorrelation structures and adjust for effects as required. For example, where correlations due to seasonal associations are observed, monthly or seasonal dummy variables will be introduced in the model. Where weekly/monthly observations are not independent of one another, we will include a correlation structure based on the most appropriate autoregressive and moving average terms (assessed using plots of autocorrelation and partial correlation). Akaike’s and Schwarz’s Bayesian information criteria will be used to select most appropriate models.

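### The claim of sufficient power at 48 or 49 monthly points has no calculation behind it; the protocol's own method gives about 75% per site, and does not describe the synthetic control estimator

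*Protocol article*

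**What the plan says.** Under *Sample size: ITS* the protocol article treats "208 weekly or 48 monthly time points" together and calls the power for medium effects sufficient. It then gives one worked example: for a slope interaction of medium size, "a sample of 208 time points has > 99% power (assuming one parameter tested and no more than five factors entered in model". The method is the G-Power module for an increase in R² in a fixed linear model. The numerical effect size, alpha and the level that counts as sufficient are not given.

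Under *Sample size: synthetic control study* the claim is repeated for monthly data: the series "provides sufficient power to detect medium effects where they exist". No calculation accompanies it. The support offered is that the number of points exceeds 40, a rule of thumb for a valid ITS analysis. The count is described as "including a one-month ‘bedding in month’), yields 49 time points".

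Under *Data collection, Synthetic control study*, the bedding-in month is handled differently: "The relevant time period is 49 months, as the month following the introduction of the PDU is excluded from the analysis".

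Under *Analytical strategy, Interrupted time series*, serial correlation is tested for first, and "If significant autocorrelation exists, we will investigate several autocorrelation structures and adjust for effects as required". Models are fitted separately at each site and the estimates are then pooled by inverse variance.

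**The concern.** A figure worked out for 208 points is used to vouch for series less than a quarter as long (208 / 48 = 4.3). This touches primary outcomes. The whole synthetic control study is monthly, including both of its primary outcomes in Table 2. *Data collection* also lets an ITS outcome be aggregated by month, with the choice made on model fit. The one calculated figure therefore covers none of the synthetic control study and perhaps not all of the ITS.

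The Discussion says that the study is well placed to show whether decision units fail to help, so null findings will inform commissioners. If one site's monthly series has roughly a one-in-four chance or more of missing a medium effect, a reader told that power is sufficient will give a null site result more weight than it can bear.

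**Working it through.** **Inputs**

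- From *Sample size: ITS*: 208 weekly or 48 monthly points, one tested parameter, at most five predictors, F test for R² increase.
- From *Sample size: synthetic control study*: 49 monthly points.
- Assumed, because not stated: f² = 0.15 (the conventional medium value for this module) and alpha = 0.05, with 0.025 and 0.10 as the range.

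**Formula.** Power = P(F′ > F₁₋α), where F′ is noncentral F with df₁ = 1, df₂ = n − 5 − 1 and noncentrality λ = f² × n.

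**Step 1: the protocol's own figure.** n = 208: λ = 0.15 × 208 = 31.2, df₂ = 202, power 99.98%. The stated figure of more than 99% is reproduced.

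**Step 2: the same method for shorter series.**

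| n | λ | df₂ | alpha 0.05 | alpha 0.025 | alpha 0.10 |
|---|---|---|---|---|---|
| 48 | 7.20 | 42 | 74.6% | 64.1% | 84.0% |
| 49 | 7.35 | 43 | 75.5% | 65.2% | 84.7% |
| 40 | 6.00 | 34 | 66.3% | 54.7% | 77.5% |

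At alpha 0.05, 80% power needs 55 points and 90% needs 73. The number of predictors hardly matters (74.8% with one predictor at n = 48). The 40-point rule itself corresponds to 66%, so exceeding it does not show adequate power.

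**Step 3: allowance for autocorrelation.** The module assumes independent errors. With lag-1 autocorrelation ρ, λ is multiplied by the ratio of the independent-error variance to the generalised least squares variance of the slope change, in a model with intercept, trend, level change and slope change. The documents give no ρ, so a range is shown (alpha 0.05).

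| ρ | ratio, n = 48 | power, n = 48 | ratio, n = 208 | power, n = 208 |
|---|---|---|---|---|
| 0 | 1 | 74.6% | 1 | 99.98% |
| 0.2 | 0.690 | 58.6% | 0.672 | 99.5% |
| 0.3 | 0.571 | 50.9% | 0.545 | 98.4% |
| 0.4 | 0.470 | 43.6% | 0.437 | 95.7% |
| 0.5 | 0.383 | 36.8% | 0.343 | 90.3% |
| 0.6 | 0.309 | 30.8% | 0.261 | 81.1% |

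**Step 4: pooling.** If four sites share one common effect, λ is multiplied by 4. At n = 48, λ = 4 × 7.2 = 28.8 and power is 99.9% with independent errors. With ρ = 0.2, 0.3 and 0.4 it is about 99%, 98% and 95 to 96% (the last depending on the denominator degrees of freedom used). Differences between sites would lower these figures.

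**Step 5: the count of months.** 24 + 24 = 48 analysed months, plus one bedding-in month = 49. Since "the month following the introduction of the PDU is excluded from the analysis", only 48 remain. The effect on power is 75.5 − 74.6 = 0.9 percentage points, so this is an inconsistency of text and not a material loss.

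**Step 6: the synthetic control.** *Analytical strategy, Synthetic control study* specifies a generalised synthetic control with parametric bootstrap intervals. Its precision depends on how well the control trusts predict the treated trust, not only on the number of months. Neither the F test nor the 40-point rule describes it.

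**The case against.** - **Pooling.** The Aims promise a combined effect, and under a common effect the pooled power is very high even with monthly data. This stands for the overall effect, and it rules out saying that the design as a whole is underpowered. But no pooled calculation is given, no assumption about heterogeneity is stated, and the Aims and the analysis section also promise estimates at each site.
- **Unstated inputs.** Alpha, sidedness, f² and a threshold are all missing, and at alpha 0.10 (one-sided 0.05) the same method exceeds 80%. This stands as a caveat: 75% is conditional. It does not rescue the claim, which cannot be checked as written.
- **Aggregation.** A fixed f² is not the same absolute effect in weeks and months. If weekly errors are independent, averaging them into months reduces noise, so the same absolute effect has a monthly f² about 4.3 times larger (0.15 × 4.33 = 0.65) and power stays above 99%. This is a fair point about absolute effects. The protocol, however, states its claim for medium effects and names no absolute effect, so f² = 0.15 applied to the series analysed is the natural reading.
- **Autocorrelation.** A reader might infer that the protocol expects autocorrelated errors and so contradicts its own calculation. The text does not say so: both the autocorrelation terms and the seasonal terms are conditional on what is found. All that can be said is that the power figure makes no allowance for something the analysis provides for.
- **The weekly figure.** A reader might also infer that the weekly claim fails. It does not: power remains above 80% up to ρ = 0.6, although it is no longer above 99% from about ρ = 0.3.

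**Conclusion.** The claim of sufficient power for monthly data is unsupported as written. By the only method the protocol gives, one site's 48-point monthly series has about 75% power for a medium effect with independent errors (f² = 0.15 and alpha 0.05 assumed; 64% to 84% over alpha 0.025 to 0.10), and about 59% to 44% if lag-1 autocorrelation is 0.2 to 0.4. These are per-site figures.

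A reader might take 75% as the power of the synthetic control study. The documents do not support that: the estimator is a different one, and its power cannot be worked out from what is given. The correct statement is that the power sentence there has no basis, not that the study has a particular lower power.

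The point is of moderate weight. The window of routine data is fixed and no estimator changes, but the text assures the reader of a property that has not been shown at site level.

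**What to change.** 1. In *Sample size: ITS*, confine the statement that "a sample of 208 time points has > 99% power" to weekly series with independent errors, give the f² and alpha used, and note that autocorrelation lowers the figure.
2. For monthly ITS series, state about 75% per site with the assumed f² and alpha. State pooled power separately, with its assumption about heterogeneity between sites.
3. Correct 49 to 48 analysed months, and reconcile *Sample size: synthetic control study* with the data collection section on the bedding-in month.
4. Delete the power sentence for the synthetic control study. Once the data are in hand, report the precision implied by the prediction error of the fitted synthetic control before the unit opened.

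The cost is a change of text, a less favourable stated figure and, for item 4, a small added analysis that has to wait for the data. No further data collection is needed.

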### Data collection

#### Interrupted time series

Outcome data will be collated as time series for 24 months pre- and 24 months post-implementation of the PDU. All data will be aggregated to a single observation at multiple time points at equal intervals. In our case, depending on the variable under study, the time series aggregation unit will be weeks or months. For out of area admissions, for example, a weekly total may be too low to appropriately use a weekly time series as differences may reflect random variation rather than a real effect (i.e. a high noise-signal ratio). The aggregation unit used will be the one that provides proportionately better model fits. Aggregated service use data over the relevant 4 years will be sourced locally from mental health trusts and the ED (acute hospital trusts) of participating PDU sites, as detailed above, through contact with Information Management & Technology (IM&T) departments at each trust. Where a substantial proportion of PDU patients (≥ 25%) are referred from a second acute trust, we will use data from that trust also. All data is handled in accordance with the UK Data Protection Act 2018 (incorporating the EU20 General Data Protection Regulation). Information Management Services personnel within the NHS Trusts will collate the trustwide service use data required for study analyses. Electronic transfer of this data between NHS Trusts and the lead university (St George’s, University of London [SGUL]) will be by encrypted email transfer. This data does not include personally identifiable information and will not be shared by SGUL with any third party or linked with other data that might render the information more identifiable. All data held on NHS or university computers will be securely held on password protected servers and not on individual PCs. The datasets generated during and/or analysed during the current study will be stored in a non-publicly available repository.

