**Primary outcome measures: ITS Study**	
Rate of informal admissions to mental health trust adult inpatient wards per 1000 trust catchment population	Rate of ED psychiatric presentations per 1000 trust catchment population)

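### Monthly ITS count outcomes treat calendar months of 28 to 31 days as equal intervals; a days-in-month exposure term would remove a small false level change and some avoidable noise

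*Protocol article*

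**What the plan says.** In Data collection (Interrupted time series), the article says that "All data will be aggregated to a single observation at multiple time points at equal intervals" and that, depending on the variable, "the time series aggregation unit will be weeks or months". The choice between them is left to fit: "The aggregation unit used will be the one that provides proportionately better model fits". Sample size: ITS gives the resulting length as "208 weekly or 48 monthly time points".

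Table 2 lists the two ITS primaries as "Rate of informal admissions to mental health trust adult inpatient wards per 1000 trust catchment population" and "Rate of ED psychiatric presentations per 1000 trust catchment population". The text introducing the table says that it specifies the denominator of each rate; for these two it is population, with no element of time. One ITS-only secondary outcome, occupied bed days, is defined as a daily mean.

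In Analytical strategy (Interrupted time series), count outcomes get a segmented Poisson or negative binomial model, and the level change at opening is a named parameter. Autocorrelation is checked first by residual plots and the Durbin-Watson test. Monthly or seasonal dummies come in if seasonal correlation is seen; otherwise, "Where no significant autocorrelation is detected, we will use a simple time series regression model".

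**The concern.** The statement about intervals is exact for weeks and untrue for calendar months: a 31-day month has 31/28 − 1 = 10.7% more time at risk than a 28-day one. A count divided by population alone therefore rises and falls with the calendar even when the daily rate is constant. In a segmented model, a February in the opening month looks like a drop at opening, and a February just before it looks like a rise.

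Two things are at stake for a monthly count series fitted without month terms:

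- a bias in the level change at a site, fixed by that site's opening month, which larger counts do not remove;
- extra residual variation, which widens standard errors.

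Both primaries could be affected, because the fit rule does not keep them weekly.

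**Working it through.** **Are these calendar months?** "Outcome data will be collated as time series for 24 months pre- and 24 months post-implementation of the PDU" gives 48 calendar months. In weeks, 4 × 52 = 208, which matches the article. Four-week blocks would give 208/4 = 52 points, not 48. So the monthly option means calendar months.

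**Feasible opening months.** Study design gives a data window from November 2012 to 31 March 2020. With 24 months needed on each side, openings run from November 2014 to April 2018: 2 + 36 + 4 = 42 months.

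**False level change.** Assume a constant daily rate and population, so the monthly count is proportional to days. For each opening month, fit by least squares

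log(days) = b0 + b1·time + b2·post + b3·post·time, with 24 + 24 points.

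Any non-zero b2 or b3 is due to month length alone. Over the 42 openings:

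| Quantity | Result |
|---|---|
| Range of b2 | −2.5% (February 2017) to +2.0% (March 2015) |
| Median absolute b2 | 0.87% |
| Openings with absolute b2 under 1% | 23 of 42 |
| Openings with absolute b2 of 2% or more | 3 of 42 (February 2015, 2017, 2018) |
| Largest absolute b3 | 0.035% a month |
| Residual SD | 2.8% |
| Durbin-Watson, no other noise | 2.64 to 3.01 |

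A segmented Poisson model gives nearly the same: −2.4% to +1.9%, median absolute 0.84%. With month dummies the largest value falls to 0.46%, which comes from the leap day.

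**Noise.** With mean monthly count m and overdispersion φ, standard errors rise by the factor √(1 + 0.0284²·m/φ). The article gives no counts, so m is assumed.

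| Events a month | φ = 1 | φ = 2 |
|---|---|---|
| 50 | +2% | +1% |
| 100 | +4% | +2% |
| 300 | +11% | +6% |
| 500 | +18% | +10% |
| 1,000 | +34% | +18% |

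**Scale against sampling error.** For this design the variance factor for b2 is 0.334, so its standard error under Poisson noise is √(0.334/m): 5.8% at m = 100, 2.6% at 500 and 1.8% at 1,000.

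**Would the autocorrelation check bring in the dummies?** In Poisson simulations (1,500 runs per setting; openings in February and June 2017), a two-sided Durbin-Watson test flagged the series in 6% of runs at 100 events a month, 9 to 11% at 500 and 13 to 22% at 1,000. Month length induces negative lag-1 correlation, so a test for positive autocorrelation would miss it.

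**Effect on the test of b2.** In the same simulations, with nominal 5% and overdispersion estimated:

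| Events a month | February 2017 (worst), no days offset | February 2017, days offset | June 2017, no days offset |
|---|---|---|---|
| 100 | 7.1% | 6.1% | 4.1% |
| 500 | 8.9% | 5.2% | 3.3% |
| 1,000 | 11.7% | 5.2% | 1.6% |

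**The case against.** **An offset is analysis-plan detail.** The article writes out no offset at all, and the full protocol and analysis plan are not shown. This is fair as far as the model goes, and a days term may well exist there. What remains is what the article itself states: equal intervals, and a denominator for the primaries that leaves out time.

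**The primaries may be weekly.** The sample-size section leads with the weekly series, and the stated reason for months is low counts. The example given, out-of-area admissions, is a proportion in Table 2, so month length largely cancels. Where counts are low, the noise cost is only a few per cent. This stands and lowers the importance. It does not remove the point, because the final rule on the unit is model fit.

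**Safeguards exist.** Real seasonality could trigger month dummies, residual and autocorrelation plots are also examined, and the interviews ask about seasonal impacts. This stands too, although month length alone would rarely trigger the dummies.

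**Pooling dilutes it.** The sign depends on the opening month. With four openings drawn at random from the 42 and equal weights (both assumptions), the pooled false level change has median 0.4% and 95th percentile 1.1%.

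**Stronger readings to avoid.** A reader might infer that a 2% error is to be expected, or that every monthly ITS series is distorted. The documents support neither. About 2% is the worst case over opening months, and series that receive month dummies are largely protected. A reader might also infer that the Durbin-Watson values of 2.6 to 3.0 would appear in practice and hide real autocorrelation. Those values are for a series with no other noise, and the masking has not been quantified.

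**Conclusion.** The point holds as a minor one. It applies to ITS count outcomes analysed by calendar month without month dummies, possibly including both primaries. There, month length gives a false level change that is typically under 1%, and 2 to 2.5% at worst. At 100 events a month the worst case is less than half of one standard error of the level change; only at counts near 1,000 a month does it reach or exceed one. The loss of precision occurs whatever the opening month and grows with the count.

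The slope change, weekly series, proportions, averages and daily mean bed days are not materially affected. In the synthetic control study the control trusts share the same calendar months, so the effect largely cancels.

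The bias figures assume a constant daily rate and population. The standard-error and error-rate figures rest on assumed event counts and on Poisson noise, or twice Poisson variance where stated. The sites' actual opening months are not given in the article, so their own bias cannot be worked out from it.

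**What to change.** For monthly ITS count outcomes, use log(catchment population × days in the month) as the offset and report rates per 1000 population per day, or per 30 days. Change the sentence on equal intervals in Data collection to say that weeks are equal, and that months are not and are adjusted for their number of days.

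The offset makes the artefact zero by construction. It needs no extra data and no extra parameters, whereas month dummies would spend 11 parameters on 48 points. Dummies can still be added where there is true seasonality. If the unshown analysis plan already has a days term, only the wording needs correcting.
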